## Abstract

**Background:**

Fetoscopic LASER coagulation of the placental anastomoses has changed the prognosis of twin-twin transfusion syndrome. However, the prematurity rate in this cohort remains very high. To date, strategies proposed to decrease the prematurity rate have shown inconclusive, if not unfavourable results.

**Methods:**

This is a randomised controlled trial to investigate whether a prophylactic cervical pessary will lower the incidence of preterm delivery in cases of twin-twin transfusion syndrome requiring fetoscopic LASER coagulation. Women eligible for the study will be randomised after surgery and allocated to either pessary or expectant management. The pessary will be left in place until 37 completed weeks or earlier if delivery occurs. The primary outcome is delivery before 32 completed weeks. Secondary outcomes are a composite of adverse neonatal outcome, fetal and neonatal death, maternal complications, preterm rupture of membranes and hospitalisation for threatened preterm labour. 352 women will be included in order to decrease the rate of preterm delivery before 32 weeks’ gestation from 40% to 26% with an alpha-error of 0.05 and 80% power.

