### Procedures, recruitment, randomisation and collection of data

The Fetal Medicine Teams in the participating centres will counsel all women being referred for suspected TTTS. When fetoscopic LASER is planned, one of the Fetal Medicine specialists will confirm that the patient fulfils the inclusion criteria, and the study will be proposed. The patients will be informed about the intended therapeutic effect and possible side effects. The patient will be given an information sheet and if possible, she will have 24 h time to reflect on participation. If they agree, after obtaining their informed consent, they will be randomised in two groups: Usual management or cervical pessary placement.

The randomisation will be computed on-line at the platform for electronic data management based at the Catalan Institute of Pharmacology (ICF) where all data will be collected in a worldwide accessible online database. Each centre will have its own randomisation list and randomisation will be 1:1 for pessary placement versus control. Only a participant identification number in the electronic database will identify the participants. All documents will be stored securely and only accessible by trial staff and authorized personnel.

The study is not blinded.

Baseline characteristics of the women, the pregnancies and issues on the TTTS and the surgery will be recorded. The cervical length will be recorded before and after surgery and every 4 weeks until delivery. We will also record complications of the surgery, complications by the pessary and perinatal results.

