### Statistics

#### Expected sample size

We based our sample size calculations on the assumption that the pessary reduces the primary outcome (preterm birth <32 weeks) from 40% in the control group to 26% in the pessary group [18]. With a study power of 80% and an alpha error of 5%, (assuming an effect size of 0.5 (moderate) and expecting a potential drop out rate of 10%), the required sample size has been estimated to be 352 patients, 176 cases in each arm of the study. We will perform 2 interim analyses, so the *p*-value would be set at 0.045 (O’Brien-Fleming rule) [23] instead of 0.05 and we would therefore need to recruit 182 patients in each arm.

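### The Abstract gives the pre-adjustment sample size of 352; with two interim analyses the protocol's own requirement is 364, a small shortfall in a core design figure

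*Protocol article*

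**What the plan says.** - **Abstract, Methods:** "352 women will be included in order to decrease the rate of preterm delivery" before 32 weeks from 40% to 26%, at alpha 0.05 and 80% power. Interim analyses are not mentioned there.
- **Expected sample size, first step:** the primary outcome is assumed to fall "from 40% in the control group to 26% in the pessary group". At 80% power and 5% alpha, with a 10% drop-out said to be expected, "the required sample size has been estimated to be 352 patients, 176 cases in each arm of the study".
- **Expected sample size, second step:** "We will perform 2 interim analyses"; for that reason the p "value would be set at 0.045" under the O'Brien-Fleming rule in place of 0.05, and "we would therefore need to recruit 182 patients in each arm". The total of 364 is not written anywhere.
- **Interim analysis:** looks are scheduled after each 100 patients, with efficacy stopping at p < 0.0001 (100 patients) and p < 0.004 (200 patients).
- **Data analysis:** significance is accepted at p < 0.05 for every analysis, with no exception for the final primary test.

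**The concern.** The interim analyses are part of the design. By the protocol's own reasoning the operative target is therefore the adjusted one, 182 per arm. The Abstract states the unadjusted total as the number that will be included and attaches 80% power to it. Readers who take the size from the Abstract and readers who take it from the Methods will expect recruitment to close at different points. If it closes at the Abstract's number, the power claimed is not the power obtained at the final level that the Methods prescribe.

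**Working it through.** **Inputs (Expected sample size, unless noted).** p1 = 0.40, p2 = 0.26, difference d = 0.14, power 80%, alpha 0.05 before and 0.045 after the interim adjustment, drop-out 10%. Allocation: "randomisation will be 1:1 for pessary placement versus control" (procedures section). Sidedness is not stated. Two-sided is assumed because it reproduces the protocol's figure; a one-sided test would give 139 per arm.

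**Formula.** Two proportions, pooled variance under the null, no continuity correction:

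n per arm = [z(1−α/2)·√(2·p̄·q̄) + z(0.80)·√(p1q1 + p2q2)]² / d²

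- p̄ = 0.33, so √(2 × 0.33 × 0.67) = √0.4422 = 0.6650
- √(0.2400 + 0.1924) = √0.4324 = 0.6576
- z(0.80) = 0.8416, so the second term is 0.5534

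**1. Reproduce the protocol's two sizes.**
- α = 0.05: z = 1.960, first term 1.3033. n = (1.8568)² / 0.0196 = 175.9, so 176 per arm and **352** in total.
- α = 0.045: z = 2.005, first term 1.3330. n = (1.8865)² / 0.0196 = 181.6, so 182 per arm and **364** in total.

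Both match exactly. The difference is 12 women, and 12/352 = 3.4%.

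**2. Power of the final test alone.** Power = Φ{[d·√n − z(1−α/2) × 0.6650] / 0.6576}
- n = 176, α = 0.05: (1.8573 − 1.3033)/0.6576 = 0.842, power 80.0%
- n = 176, α = 0.045: (1.8573 − 1.3330)/0.6576 = 0.797, power **78.7%**
- n = 182, α = 0.045: (1.8887 − 1.3330)/0.6576 = 0.845, power **80.1%**

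**3. Counting the interim looks.** 400,000 simulated trials per setting, pooled z-test, looks at 100 and 200 patients with the protocol's thresholds, no futility stopping. Type I error was simulated at 40% in both arms.

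| Total | Final level | Power | Type I error |
|---|---|---|---|
| 352 | 0.045 | 79.2% | 0.046 |
| 364 | 0.045 | 80.4% | 0.048 |
| 352 | 0.05 | 80.0% | 0.052 |
| 364 | 0.05 | 81.6% | 0.050 |

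**4. Drop-out, a separate matter.** 176 and 182 come straight from the formula, so neither contains an allowance for loss. With 10% loss and the final level at 0.045:
- 352 enrolled: 176 × 0.9 = 158.4 per arm, power 74.3% (74.2% with 158)
- 364 enrolled: 182 × 0.9 = 163.8 per arm, power 75.7% (75.8% with 164)
- A size carrying both adjustments would be 182/0.9 = 202.2, so 203 per arm or 406 in total.

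**The case against.** Several counter-arguments have force.

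- **The Methods are not in conflict with themselves.** The Expected sample size section gives a base figure, a reason and an adjusted figure. A reader might infer two rival targets within that section. The text does not support this: 352 is an intermediate result there, and the mismatch lies between the Abstract and the Methods. This stands.
- **Alpha 0.05 in the Abstract is defensible.** A reader might infer that it must become 0.045. An overall error rate of 0.05 is compatible with a final nominal level of 0.045 in a group-sequential design, and the simulated overall error under the stated thresholds is 0.046 to 0.049 across the settings run at 0.045, with and without drop-out. The Abstract's alpha is incomplete, not wrong. This stands.
- **The power loss is small.** It is 1.3 points for the final test alone and less than one point once the looks are counted. It is tempting to quote about 74% for 352 after drop-out as the damage done, but 364 gives about 76% after the same loss. Nearly all of that fall comes from the missing drop-out allowance. This stands.
- **The stopping rules hardly depend on the total.** The looks are fixed by patient count with explicit p-values. The second falls at 200/352 = 56.8% or 200/364 = 54.9% of the total.
- **An abstract may simplify.** It may leave out the interim analyses, but it should not give as the number to be included one that the Methods go on to replace. The conditional wording about 182 per arm does not rescue 352, because its condition, two interim analyses, is stated as planned and is scheduled.
- **With p < 0.05 at the end, 352 would deliver 80.0%.** That reading follows the Data analysis section, but it contradicts the explicit replacement of 0.05 by 0.045 in the sample size section.

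**Conclusion.** The point holds as an inconsistency in a core design figure with a modest numerical effect. The Abstract's 352 is superseded by the Methods' 182 per arm (364). At 352 and a final level of 0.045, power before drop-out is about 79%, against the stated 80%. The documents do not support calling this a serious loss of power.

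Two neighbouring points belong with the correction. The Data analysis section still applies 0.05 to every test, so the final primary test has two stated thresholds; the effect on overall error is slight (0.050 to 0.052 in the table), but only one rule can be followed. And moving to 364 does not secure 80% if the expected 10% drop-out occurs, because neither total allows for it.

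The figures assume a two-sided, uncorrected pooled test, the 40% and 26% rates, looks at 100 and 200 with the published thresholds, and no stopping for futility.

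**What to change.** 1. **Abstract:** replace 352 with 364 women (182 per arm), and state an overall two-sided alpha of 0.05 with a final-analysis level of 0.045 after two interim analyses.
2. **Expected sample size:** write out the total of 364 beside 182 per arm.
3. **Data analysis:** except the final primary test from the general 0.05 threshold and give 0.045 for it.
4. **If 352 is kept:** state about 79% power before drop-out.
5. **Drop-out:** remove the statement that 10% was allowed for, or restate the power after that loss (about 74% with 352, about 76% with 364).

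Items 1 to 3 are wording only: 364 is already what the Methods require, although it is 12 women more than the Abstract announces. Items 4 and 5 are also changes of text.

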**Discussion:**

The trial aims at clarifying whether the cervical pessary prolongs the pregnancy in cases of twin-twin transfusion syndrome regardless of cervical length at the time of fetoscopy.

**Trial registration:**

ClinicalTrials.gov Identifier: NCT01334489. Registered 04 December 2011.

## Background

Fetoscopic LASER coagulation of placental anastomoses (FLC) with or without Solomon technique [1] is the treatment of choice for severe Twin-to-Twin Transfusion Syndrome (TTTS) [2]. This procedure completely changed the natural history of TTTS [3]. However, although this first and most important step was taken and survival rates and neurological outcomes improved, premature births remain a serious concern: 41% of patients will deliver before 32 completed weeks [4]. Therefore, an effort to reduce prematurity is required. Cervical pessary placement could constitute an option to reduce prematurity, regardless of cervical length at the time of fetoscopy.

Transvaginal ultrasound permits the identification of twin pregnancies at high risk of preterm delivery [5, 6]. It is known that cervical length (CL) plays a role in the onset of preterm birth. The pathophysiology of premature ripening of the cervix varies between singleton and multiple pregnancies with twin pregnancies having a higher prevalence of short cervix at 23 weeks [7]. Regarding TTTS, Yamamoto et al. showed that short CL before treatment is an independent risk factor for preterm delivery [8].

The prematurity rate in cases of severe TTTS in patients with long cervix treated by FLC remains very high [9–11]. Although many cases are delivered prematurely for medical indications (mainly selective intrauterine growth restriction), a large proportion will also develop spontaneous preterm labour [12].

Information is lacking regarding the best therapeutic option in patients with short cervix who also require fetoscopy [9–11]. Salomon et al. suggested the use of an emergency cerclage in cases of TTTS with a short cervix at the time of surgery [13]. In this observational study, the emergency cerclage could prolong pregnancy and improve perinatal outcomes. It was the first study to demonstrate a potential benefit to prevent premature delivery in such cases. Nevertheless, emergency cerclage continues to be an invasive procedure requiring anaesthesia. It also bears the risk of infection, local inflammatory reactions and premature rupture of membranes, although these were not observed in the Salomon study [14–16]. In current practice an emergency cerclage is usually performed for a cervical length less or equal to 15 mm after fetoscopic surgery in cases of TTTS, although the benefit of the cerclage in these cases has been recently questioned [17].

Previous studies in singleton and twin pregnancies showed that the use of a cervical pessary significantly reduces the frequency of birth before 32 weeks and prolongs the pregnancy [18–20]. The advantages of using a cervical pessary are that it is a non-invasive, operator-independent, easy to use device, does not require anaesthesia and can easily be removed when necessary.

Our group performed a pilot study in which we placed an Arabin cervical pessary in cases of TTTS with FLC and retrospectively compared the outcomes with a control group. There was a lower rate of preterm birth and less neonatal morbidity in the pessary group [21].

The ProTWIN Trial [22], despite concluding that in unselected women with multiple pregnancies prophylactic use of a cervical pessary does not reduce poor perinatal outcome, found a significant difference in perinatal outcome for the subgroup of monochorionic pregnancies (14% vs. 25% in the control group).

The aim of this trial is to investigate whether a prophylactic cervical pessary will lower the incidence of preterm delivery in cases of twin-twin transfusion syndrome requiring fetoscopic laser coagulation.

## Methods/design

### Aims

We will perform a randomised trial (the PECEP LASER Trial: Arabin Cervical Pessary for prevention of preterm birth in cases of Twin-to-Twin Transfusion Syndrome treated by Fetoscopic Laser coagulation) to assess the effect of the Arabin cervical pessary on the rate of preterm delivery in cases of monochorionic pregnancies with twin-twin transfusion syndrome requiring fetal therapy.

This is a multicenter study to be conducted in the Hospital Universitari Vall d’Hebron in Barcelona (Catalunya, Spain), the Universitaire Ziekenhuizen in Leuven (Belgium), and the University Medical Centrer Hamburg-Eppendorf (UKE) in Hamburg (Germany). All centers have approval from the respective Medical Ethics Committees to conduct the trial.

The trial was registered in ClinicalTrials.gov in December 4th, 2011 (https://www.clinicaltrials.gov/ct2/show/NCT01334489?term=NCT01334489&recrs=a&rank=1). The trial identifier is NCT01334489.

The study is open for other centres who wish to participate.

### Participants

All women presenting with a monochorionic-diamniotic pregnancy with severe twin-twin transfusion syndrome between 16 and 26 weeks are eligible for the study with the exception of pregnancies complicated by major congenital abnormalities, uterine malformations, placenta praevia, active vaginal bleeding or spontaneous rupture of membranes at the time of randomization. Also patients with contraindication for pessary placement as painful regular uterine contractions, or a cervical cerclage in place will be excluded [20], as well as cases of demise of both twins after surgery.

Gestational age will be determined through menstrual history and first trimester scan.

### Procedures, recruitment, randomisation and collection of data

The Fetal Medicine Teams in the participating centres will counsel all women being referred for suspected TTTS. When fetoscopic LASER is planned, one of the Fetal Medicine specialists will confirm that the patient fulfils the inclusion criteria, and the study will be proposed. The patients will be informed about the intended therapeutic effect and possible side effects. The patient will be given an information sheet and if possible, she will have 24 h time to reflect on participation. If they agree, after obtaining their informed consent, they will be randomised in two groups: Usual management or cervical pessary placement.

The randomisation will be computed on-line at the platform for electronic data management based at the Catalan Institute of Pharmacology (ICF) where all data will be collected in a worldwide accessible online database. Each centre will have its own randomisation list and randomisation will be 1:1 for pessary placement versus control. Only a participant identification number in the electronic database will identify the participants. All documents will be stored securely and only accessible by trial staff and authorized personnel.

The study is not blinded.

Baseline characteristics of the women, the pregnancies and issues on the TTTS and the surgery will be recorded. The cervical length will be recorded before and after surgery and every 4 weeks until delivery. We will also record complications of the surgery, complications by the pessary and perinatal results.

### Intervention

For women allocated into cervical pessary group, the device will be inserted within 72 h after fetal surgery in the assessment room of the outpatients Department. This procedure does not require anaesthesia and does not need to be performed in an operating theatre.

All patients, both the pessary and the expectant management group, will be followed as in routine monochorionic follow-up, with clinical clinical review and ultrasound every two weeks. We will perform a transvaginal ultrasound for measuring cervical length every four weeks and will also assess the correct placement of the pessary.

Further surveillance of the pregnancy will not be influenced by the participation in the study. If the cervical length decreases later on during the pregnancy, the gestation will be managed according to the local protocol. However, cervical cerclage or progesterone will not be allowed in any case during the rest of the pregnancy.

The pessary will be removed at 37 weeks of gestation or before if any unexpected event or spontaneous delivery occurs. The indications to remove the pessary before this time will be: active bleeding, persistent contractions after tocolysis and premature rupture of the membranes after 34 weeks. After removing the pessary, the obstetrical management will be done as usual.

The study will close after the home discharge of the last newborn, as neonatal adverse outcomes will also be recorded.

### Outcomes

The primary outcome will be delivery before 32 completed weeks.

Secondary outcomes will be related to the delivery and perinatal results: preterm delivery before 28, 30, 34 and 37 weeks; preterm rupture of membranes; hospitalisation for threatened preterm labour (including the need of tocolysis and fetal lung maturation); fetal or neonatal death; composite neonatal morbidity (any of intraventricular haemorrhage, necrotising enterocolitis, retinopathy of prematurity, proven or suspected sepsis, need of Neonatal Intensive Care, need of ventilation, phototherapy, antibiotics or blood transfusion). We will also record significant maternal adverse effects, mainly due to the pessary.

A long-term follow-up of the babies is not planned.

### Statistics

#### Expected sample size

We based our sample size calculations on the assumption that the pessary reduces the primary outcome (preterm birth <32 weeks) from 40% in the control group to 26% in the pessary group [18]. With a study power of 80% and an alpha error of 5%, (assuming an effect size of 0.5 (moderate) and expecting a potential drop out rate of 10%), the required sample size has been estimated to be 352 patients, 176 cases in each arm of the study. We will perform 2 interim analyses, so the *p*-value would be set at 0.045 (O’Brien-Fleming rule) [23] instead of 0.05 and we would therefore need to recruit 182 patients in each arm.

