#### Data analysis

A descriptive analysis by preterm birth will be carried out calculating means and medians for quantitative variables and proportions for categorical variables. T-test or Mann-Whitney test and Pearson Chi-squared or Fisher test will be used for comparing among exposure and outcomes groups per pregnancy. A multivariate logistic regression will be fitted to control for possible confounders. Relative risks and 95% confidence interval will be calculated for the outcomes.

For fetal and neonatal outcomes, multilevel models will be used to analyse continuous outcomes and generalized estimating equations will be used to assess categorical outcomes to adjust for the clustering of twins in mothers. A secondary analysis of length of gestation after fetoscopy will be plotted on a staggered-entry Kaplan-Meier curve where gestational age at birth (in days) will be the final event. Elective A Mantel-Cox test will be performed to test statistically for significant differences in the time interval between fetoscopy and birth. All analyses will be carried out with SPSS® 19.0 statistical package (IBM Company SPSS Inc. Headquarters, Chicago, Illinois. USA). Statistical significance will be accepted in all cases with a *p* < 0.05.

We do not expect to have lost data because this study has a short follow-up time. We will also perform a per-protocol analysis.

We also intend to perform a subgroup analysis according the cervical length: over 25 mm, 15 to 25 mm and less than 15 mm. We decided to perform the subgroup analysis with these cut-off lengths because 25 mm is around the 5th centile for cervical length for twins less than 22 weeks’ gestation [24] and some groups perform cervical cerclage in TTTS patients with CL below 15 mm [13].

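### The sample size contains no 10% drop-out allowance: 176 and 182 per arm are both zero-loss numbers, so with 10% loss power is about 74–76%, not 80%

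*Protocol article*

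**What the plan says.** All the inputs are in the Expected sample size section of the protocol article. The primary outcome, birth before 32 weeks, is assumed to fall "from 40% in the control group to 26% in the pessary group". The design values are given as "With a study power of 80% and an alpha error of 5"%. In the same sentence the protocol adds "assuming an effect size of 0.5 (moderate") and then "expecting a potential drop out rate of 10%), the required sample size has been estimated to be 352 patients", which is 176 per arm.

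The section then turns to the two interim analyses, "so the *p*-value would be set at 0.045 (O’Brien-Fleming rule"), and concludes "we would therefore need to recruit 182 patients in each arm", which is 364 in total. The Abstract repeats 352 women with the same rates, alpha and power, and does not mention drop-out.

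On missing outcomes, the Data analysis section states: "We do not expect to have lost data because this study has a short follow-up time".

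**The concern.** A reader will take the paragraph to mean that the trial keeps 80% power even if one woman in ten is lost. If the inflation was never applied, that protection does not exist. Anyone interpreting a null result would then credit the trial with more power than it had under its own attrition assumption.

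Two further statements do not fit. An effect size of 0.5 is not what 40% versus 26% amounts to on the usual scale for proportions. And an expectation of no lost data sits badly beside a 10% drop-out rate.

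**Working it through.** **Inputs** (Expected sample size section, except where noted): p1 = 0.40, p2 = 0.26, difference 0.14, power 80% (z = 0.8416), alpha 0.05 and then 0.045, drop-out 10%. Allocation is 1:1 (Procedures, recruitment, randomisation and collection of data). Sidedness is not stated. Two-sided is assumed because it reproduces both figures (z = 1.9600 and 2.0047).

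**Step 1: reproduce the protocol's figures with no drop-out.** Pooled-variance formula, per arm:

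n = [z_alpha × √(2 p̄(1−p̄)) + z_power × √(p1(1−p1) + p2(1−p2))]² / (p1−p2)²

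Here p̄ = 0.33, so √(2 × 0.33 × 0.67) = 0.6650, and √(0.24 + 0.1924) = 0.6576.

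- Alpha 0.05: (1.9600 × 0.6650 + 0.8416 × 0.6576)² / 0.0196 = 175.9, so **176** per arm. This is the protocol's figure.
- Alpha 0.045: (2.0047 × 0.6650 + 0.8416 × 0.6576)² / 0.0196 = 181.6, so **182** per arm. This is also the protocol's figure.

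The rise from 176 to 182 is explained entirely by the change in alpha and hides no attrition margin.

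**Step 2: add the 10% allowance, n/(1 − 0.10).**

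- 176/0.9 = 195.6, so 196 per arm (392 in total).
- 182/0.9 = 202.2, so 203 per arm (406 in total).

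**Step 3: does another formula give 176 with the allowance included?** At alpha 0.05 and 40% versus 26%, per arm:

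| Variant | No loss | With 10% loss |
|---|---|---|
| Two-sided, pooled | 176 | 196 |
| Two-sided, unpooled | 174 | 194 |
| Two-sided, arcsine | 176 | 196 |
| Two-sided, simple pooled | 178 | 198 |
| Two-sided, continuity-corrected | 190 | 212 |
| One-sided, pooled | 139 | 155 |
| One-sided, continuity-corrected | 153 | 170 |

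No variant with the allowance is within 3% of 176. The nearest, one-sided with continuity correction, gives 170 at 0.05 and 177 at 0.045, so it misses both stated figures. The two-sided zero-loss calculation matches both to the patient.

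**Step 4: power after 10% loss.** Power = Φ[(0.14√n − z_alpha × 0.6650)/0.6576].

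| Enrolled per arm | Evaluable per arm | Alpha | Power |
|---|---|---|---|
| 176 | 158.4 | 0.05 | 75.7% |
| 176 | 158.4 | 0.045 | 74.3% |
| 182 | 163.8 | 0.045 | 75.7% |
| 182 | 163.8 | 0.05 | 77.1% |

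Summing exact binomial probabilities for the uncorrected chi-squared test agrees: 75.7% (158 per arm, 0.05), 74.5% (158, 0.045) and 75.8% (164, 0.045). With no loss, power is 80.0% for 176 at 0.05 and 80.1% for 182 at 0.045.

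**Step 5: the effect size.** Cohen's h = 2 arcsin√0.40 − 2 arcsin√0.26 = 0.30. The relative risk is 0.26/0.40 = 0.65, and the odds ratio is (0.26/0.74)/(0.40/0.60) = 0.53. A standardised effect of 0.5 would need 2 × (2.8016/0.5)² = 62.8, so 63 per arm. If 0.5 was meant as an odds ratio, the pessary rate would be 25% and n would be 152 per arm (169 with 10% loss). Neither reading yields 176.

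**The case against.** The strongest reply is that the shortfall is conditional: power falls only if the 10% have no primary outcome. The endpoint is the timing of delivery, which is usually known even for a woman who stops using the pessary. The Discussion calls this an intention-to-treat study, and the Data analysis section expects no missing data. On that expectation 182 per arm gives 80.1% power at 0.045. Drop-out might also mean stopping the pessary rather than losing the outcome, in which case the two statements need not conflict outright.

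The condition is real and should be stated. It does not rescue the paragraph, which chose 10% and says the total allows for it. If drop-out means non-adherence, no allowance for that is in 176 or 182 either, and dilution under intention to treat would also cost power. If no loss is expected, the 10% clause is what is wrong.

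Three smaller points are fair:

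- The 74% end pairs the Abstract's 352 with alpha 0.045. The pairings the sample-size section itself makes both give about 76%.
- Inflating the unrounded 181.6 gives 202 per arm rather than 203, which is a rounding convention.
- The 0.5 effect size is not needed to obtain 176 or 182, so correcting it is secondary.

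**Conclusion.** The concern holds. Both stated sample sizes are zero-loss numbers, and the 10% drop-out allowance claimed for them is absent. Under the protocol's own 10%, power is about 76% for the N and alpha pairings in the sample-size section, and about 74% if 352 women are tested at 0.045. The type II error is then about 25% rather than 20%.

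This rests on a two-sided test and on the 10% having no primary outcome. If nobody is lost, 80% power is correct and the drop-out clause is false, so the paragraph is wrong as written either way. Type I error and bias are not affected. The correction matters because this is the statement on which the trial's power is judged.

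**What to change.** Choose one of two wordings for the Expected sample size section:

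- State that 182 evaluable women per arm give 80% power for 40% versus 26% at two-sided 0.045, that no drop-out allowance is included, and that power is 76% with 10% loss.
- If no loss of the primary outcome is expected, as the Data analysis section says, delete the 10% clause.

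Whichever is chosen, make the two sections agree and say what drop-out means (missing outcome or stopping the pessary). Delete the effect size of 0.5, or replace it with the values that belong to 40% versus 26%: h = 0.30, relative risk 0.65, odds ratio 0.53. Bring the Abstract's 352 into line with the final target.

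The cost is a few sentences and, if the 10% is kept, a slightly less favourable power statement. No extra patients are required. Enrolling 203 per arm would be needed only if the sponsor wished to keep 80% power with 10% loss.
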